
#### Organization of ad hoc data collection

The ad hoc collections at inclusion and throughout patient follow-up will be carried out by trained IRCs. They will produce the compilations necessary for the classification of rehospitalizations in medicine or surgery departments, as well as the research of the lost-to-follow-up. IRCs will be near to participating health facilities to maximize their responsiveness for patient inclusion and ad hoc collection at inclusion.

##### Ad hoc collection of sequelae and elements of pathways

◦ **At inclusion (during hospitalization)**

IRCs go to the site at the end of the patient’s stay in order to proceed with inclusion. This collection is done directly with the patient or when the patient is unable to cooperate, with the entourage or the hospital care team. The information collected will be: 1) patient’s postal address at the end of his hospitalization, his telephone number in order to carry out the follow-up visit at 3 months and 1 year after the acute phase as well as the name and address of his attending physician (potentially important information in the search for those lost to follow-up), 2) life pathway before stroke data, 3) administration of three specific assessment scales for different dimensions of sequelae at discharge: NIHSS, BI and mRS.
◦ **Follow-up visit at 3 months and 1 year after the acute phase by phone and by mail**

This follow-up at 3 months and 1 year will be carried out by the IRCs, in 2 steps and 2 modes of collection: a mailing and a telephone interview.
First step: a mail will be sent by the IRC 15 days before the anniversary dates of the 3 months and 1 year after the acute episode. It contains: 1) patient information document about the survey, 2) self-assessment scales exploring different dimensions of sequelae to be completed by the patient (self-questionnaire) or by a caregiver according to the patient’s state of health: FSS, HADS, CIQ-R, 3) explanations about modality of filling in self-questionnaires, 4) pre-stamped envelope to return the self-questionnaires. Patients will have 15 days to complete the questionnaires and return them.Second step: telephone interview will be conducted in the week following the anniversary dates of the 3 months and 1 year post-stroke. If the mail questionnaires have not been received, this phone call will serve as a reminder. In case of no answer, the IRC will repeat its call up to 5 times. After 5 attempts, the patient will be considered as lost-to-follow-up.

The information collected will be: 1) life pathway after-stroke data, 2) administration of three specific assessment scales for different dimensions of sequelae: F-TICS-m, Barthel Index and mRS.

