### Data sources and data collection

#### Data sources

Three types of data sources are considered (Table 1):

**Table 1 Tab1:** Summary of Stroke Patient Data Collection – PAPASéPA

	Inclusion visit	Follow-up at 3 months post-stroke	Follow-up at 1 year post-stroke
Verification of eligibility criteria	✓		
Patient information^1^ + Oral consent	✓		
Data on the care, socio-demographic and clinical pathways (history, severity, complication during the stay ...) to the acute phase (pre-hospitalization and hospitalization) from the ObA2 Observatory ^2^	✓		
Hospitalization data, consultations, acts, outpatient care from the SNDS^3^	Continuous collection		
Clinical data (ad hoc collection):			
- Severity of stroke: NIHSS at discharge	✓		
- Risk factors (alcohol)	✓		
Stroke pathways data (ad hoc collection)^4^			
- Patient referral ^4^	✓		
- Level of education ^5^	✓		
- Professionnal activity ^5^	✓		
- Marital status ^5^	✓	✓	✓
- Cohabitation status ^5^	✓	✓	✓
- Ability to drive ^5^	✓	✓	✓
- Place of life ^5^	✓	✓	✓
- Participation in a therapeutic education program ^5^		✓	✓
- Medical and social care ^5^		✓	✓
- Allowances for disability ^5^		✓	✓
- Family/Caregiver ^5^		✓	✓
- Development and technique to improve autonomy and home care ^5^		✓	✓
- Technical assistance for walking ^5^		✓	✓
- Legal background ^5^		✓	✓
Sequelae post-stroke (ad hoc collection)			
Cognitive disorders (TICS*) ^5^		✓	✓
Anxiety-depressive disorders (HADS**)(Self-assessment)^6^		✓	✓
Fatigue (FSS***) (Self-assessment)^6^		✓	✓
Activity limitations (BI ǂ) (Self-assessment)^6^	✓	✓	✓
Activity limitations (MRSǁ) ^5^	✓	✓	✓
Participation restriction (CIQ-R§) (Self-assessment) ^6^		✓	✓

*Telephone Interview for Cognitive Status; **hospital anxiety and depression scale; ***Fatigue Severity Scale; ǂBarthel Index; ǁmodified Ranking scale; §Community Questionnaire

^1^ Address; telephone number

^2^ Type of stroke; Severity (NIHSS) at admission; Gender; Age; History of Neuro-cardiovascular; History of neuropsychiatric disorders; Anticoagulant / antiaggregant treatments; Rankin before stroke; Date/time start of symptoms; Date/ time call to general practitioner; Date/time call to emergency medical services; Place of occurrence of the stroke; Mode of transport; Date/time of admission to hospital; Type of hospitalization unit; Performing thrombolysis / tele-thrombolysis / thrombectomy; Type of antithrombotic treatment; Complication during stay; duration of stay

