^3^ Number / type / duration of hospitalization in medicine or surgery, rehabilitation, psychiatry departments. Hospitalization at home; Number / type of medical and paramedical consultations at hospital; Medical ambulatory care: number / type of medical consultations (general practitioner, neurologist, functional rehabilitation physician, cardiologist) and number of care periods, total duration of each care period / type of paramedical consultations (physiotherapy; speech therapy; orthopsy); Quantity of drug deliveries (antiaggregant, antihypertensive, statin or anticoagulant treatment, analgesic), external medical consultations for neurology, rehabilitation, cardiology in health institutions; Vital status of patients

^4^ Patient referral (admission to the hospitalization area of the institution, transfer to another institution), Level of education (INSEE classification); Marital status (Married - Accessed - Partner; Separated - Divorced – Widowed; Single); Cohabitation status (couple; in family- friends; institution), Ability to drive (yes, no); Place of life (home, institution, medico-social structure), Medical-social care (services to support social life, services to help and support at home, services to provide nursing care at home, services to provide medical and social support), Family/Caregiver (yes, no); Development and technique to improve autonomy (yes, no); Legal background (Curatorship, Guardianship)

^5^ Data collected by telephone by the nurse

^6^ Postal delivery to the participant’s home

Extraction of data from two existing databases: the ObA2 cohort and the French National Health Data System (*Système National des Données de Santé* – SNDS). The extractions from existing databases will provide the main information about care pathways, patient characteristics and stroke characteristics.

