◦ Number / type / duration of hospitalization in medicine or surgery departments, rehabilitation department, psychiatry department and hospitalization at home. Hospitalisations will be classified into three categories corresponding to hospital stays with different clinical meanings with regard to the evolution of stroke (readmission for management of stroke recurrence and post-stroke complications, readjustment for post-stroke follow-up and secondary prevention of stroke and re-hospitalizations to manage a clinical situation not related to stroke);◦ Number / type of medical and paramedical consultations at hospital;◦ Medical ambulatory care: number / type of medical consultations (general practitioner, neurologist, functional rehabilitation physician, cardiologist) and of paramedical consultations (physiotherapy, speech therapy, orthopsy), number of care periods, total duration of each care period;◦ Quantity of drug deliveries (antiaggregant, antihypertensive, statin or anticoagulant treatment, analgesic);◦ Vital status of patients.

**Ad hoc collection** at any of three points in the study (initial episode, at 3 months and 1 year after the initial episode).

The collection time for each variable is specified in Table 1. The categories of variables collected are as follows:
◦ **Clinical data:** risk factors (Alcohol), severity of stroke at discharge (NIHSS)◦ **Stroke life pathways data:** patient referral, level of education, marital status, cohabitation status, professional activity, ability to drive, place of life, participation to a therapeutic education program, medical and social care, allowances for disability, presence of family and caregiver, development and technique to improve autonomy and home care, technical assistance for walking, legal background.◦ **Post-stroke sequelae assessment**

A selection of scales measuring each of the dimensions explored in our project was selected, based on elements of feasibility, frequency of use in the exploration of the dimension considered and metrological performance (validity and reproducibility): The mode of collection of sequelae has been adapted according to the validated mode of administration for each of the scales. The following sequelae are assessed:

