**Cog impairment** using the **French Telephone Interview for Cognitive Status Modified (F-TICS-m).** The TICS scale is a tool for screening for memory disorders. It evaluates time orientation, spatial orientation, immediate memory, calculation, semantic memory, delayed recall, language, understanding of an instruction. Cut offs of 24 and 34 are used (a score less than 24 corresponds to dementia, a score between 24 and 33 corresponds to mild cognitive impairment and a score more than 34 corresponds to a normal condition). This scale was validated in French by telephone [19].**Depression and anxiety** using the **hospital anxiety and depression scale (HADS)**. The anxiety and depression score through the HADS seeks to identify an anxiety-depressive symptomatology and assess its severity. It is composed of 14 items divided into 2 scores of seven items each: a depression score (one for dysphoria, one for deceleration and five for the anhedonic dimension) and an anxiety score. Each item is rated from 0 to 3, allowing to obtain 2 scores. The maximum score for each score is 21. This scale was validated in French by telephone and in a self-administered collection mode [20].**Fatigue** using the **Fatigue Severity Scale (FSS).** The fatigue score through the FSS measures the impact of fatigue on different functions. This is a short questionnaire of nine questions, to which the patient answers on a scale from 1 to 7. The overall score is the average of all the scores obtained on each of the 9 questions. The higher the result, the greater the fatigue. A threshold of 5.5 is often used to differentiate high and low fatigue. This scale was validated in French in a self-administered collection mode [21].**Genito-sexual disorders** using closed-ended question “yes/no”.**Limitations of activities** using the **modified Rankin Scale (mRS)** [23] and the **Barthel Index (BI)** [22]. The modified Rankin Scale (mRS) and the Barthel Index (BI) are commonly used scales measuring the actual abilities of the stroke patient in the basic activities that determine autonomy. The mRS is a more global scale, which measures functional independence rather than the performance of specific tasks. In this way, mental as well as physical adaptations following neurological deficits are assessed. The scale consists of 7 levels, from 0 to 6, with 0 corresponding to no symptoms and 6 corresponding to death. Cut offs of 2 is used (a score less than or equal to 2 corresponds to independence, a score greater than 2 corresponds to dependence). This scale was validated in French by telephone and in self or hetero-administered data collection mode. The IB was developed in 1965 [22] and later modified by Granger and colleagues [43] to measure patient performance in 10 activities of daily living. The IB is considered a sensitive and reliable disability scale for stroke patients. The IB items can be divided into two groups: one, related to self-care (diet, grooming, bathing, clothing, urinary and anal continence, and toilet use) and the other, related to mobility (ambulation, transfers and stair climbing). The maximum score is 100, which indicates that the patient is totally independent in physical functioning. The lowest score is 0, which represents a totally dependent bedridden state. A dependency to consider a return home is usually defined by a score greater than or equal to 60. The IB is a scale validated in French in a data collection mode by interview (hetero-administered).**Participation restrictions** using the **Community Integration Questionnaire (CIQ)**. The CIQ assesses disability for brainy people in three areas: home integration (active participation in the functioning of the home or household), social integration (participation in social activities outside the home), productivity (regular work performance). It is composed of three sub-scores: home integration [0–12], social integration [0–10], productivity [0–7]. The total CIQ score [0–29] is the sum of the 3 sub-scores.

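### Caregivers may complete the HADS, FSS and CIQ-R, against the plan's own statements on mode, and no listed variable shows who answered, so caregiver associations may partly reflect the rater

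*Protocol article*

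**What the plan says.** All references are to the protocol article; no statistical analysis plan is shown.

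- **Who completes the forms** (Ad hoc collection of sequelae and elements of pathways). The mailing at 3 months and 1 year contains the FSS, HADS and CIQ-R, "to be completed by the patient (self-questionnaire) or by a caregiver". The stated trigger is the patient's health. The article does not define a caregiver or say whether the caregiver writes down the patient's answers or gives a judgement.
- **Mode of collection** (Data sources and data collection). "The mode of collection of sequelae has been adapted according to the validated mode of administration for each of the scales". For the FSS: "This scale was validated in French in a self-administered collection mode". For the HADS: "This scale was validated in French by telephone and in a self-administered collection mode". No validated mode is given for the CIQ. Table 1 labels all three as self-assessment, delivered by post.
- **Caregiver as a pathway variable.** The life-pathway data include "presence of family and caregiver", coded yes or no and collected at 3 months and 1 year. Cohabitation status and place of life are also collected.
- **Use of the scales.** Secondary objective 1 relates pathway components to cognitive disorders, anxiety and depression, fatigue and participation. Evaluation criteria defines each scale once, without reference to the respondent. Analysis plan names regression models with random effects. Analysis strategy uses available data, with optional multiple imputation for the primary endpoint only.

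**The concern.** Anxiety and depression are largely internal states that another person has to infer, and the same is partly true of fatigue. If caregivers rate systematically higher or lower than patients would, the scores of patients with a caregiver shift for a reason unrelated to the patient's condition. A patient without a caregiver cannot be rated in this way. The difference would then appear as an association between having a caregiver, living with someone or living in an institution and the outcome, which is the kind of result secondary objective 1 is meant to produce.

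Adjusting for stroke severity would not remove this. At the same NIHSS a patient with a caregiver can be rated by proxy and a patient without one cannot. A patient too unwell to answer and without help may also return no form, and would then drop out of an available-data analysis. Recording the respondent matters at the collection stage: if it is not captured then, no later analysis plan can separate the raters.

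**Working it through.** **1. Do the statements on mode agree?**

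| Scale | Validated mode stated | Table 1 label | Follow-up procedure | Conflict |
|---|---|---|---|---|
| FSS | self-administered | self-assessment | patient or caregiver | with the validated-mode statement and with Table 1 |
| HADS | telephone, self-administered | self-assessment | patient or caregiver | with the validated-mode statement and with Table 1 |
| CIQ-R | none given | self-assessment | patient or caregiver | with Table 1 only |

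**2. Is the rater linked to an exposure under study?** Yes, indirectly. State of health decides whether a caregiver is needed; availability decides whether one can complete the form. Caregiver presence is thus a necessary condition for a proxy rating, and it is also a component to be tested against the same scales.

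**3. Can the raters be separated later?** Table 1 lists the ad hoc variables in some detail. None is the identity or role of the respondent.

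**4. How large could the effect be?** The article gives no figure for the share of forms completed by caregivers or for the difference between caregiver and self-rating, so there is no plan figure to reproduce. Everything below is assumed, to show a range.

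Assume that the true prevalence of a HADS depression score of 8 or more is 30% with and without a caregiver, and that proxies occur only where there is a caregiver. Let s be the share of caregiver-present forms that are proxy-rated, and q the prevalence that proxies report.

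Observed prevalence with a caregiver: p1 = (1 − s) × 0.30 + s × q

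Spurious odds ratio: OR = [p1/(1 − p1)] / [0.30/0.70]

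| s | q | p1 | OR |
|---|---|---|---|
| 0.20 | 0.45 | 0.24 + 0.09 = 0.33 | 1.15 |
| 0.40 | 0.45 | 0.18 + 0.18 = 0.36 | 1.31 |
| 0.60 | 0.45 | 0.12 + 0.27 = 0.39 | 1.49 |
| 0.40 | 0.20 | 0.18 + 0.08 = 0.26 | 0.82 |

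**5. What would that do to a test at 5%?** Assume further that half the patients have a caregiver and that proxies raise the prevalence by 10 points (q = 0.40). The totals are those in Sample size selection: 368 per stratum and 1104 overall. The rejection rate is that of a two-sided comparison of two proportions when there is no true association.

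| s | OR | Rejection rate, N = 368 | Rejection rate, N = 1104 |
|---|---|---|---|
| 0.10 | 1.05 | 5.5% | 6.5% |
| 0.30 | 1.15 | 9.5% | 19% |
| 0.50 | 1.26 | 18% | 43% |

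Only survivors can contribute these scales. With the plan's assumed 19% mortality, 1104 becomes 1104 × 0.81 = 894, so the last column somewhat overstates the rates.

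**The case against.** - **Pooling is not stated.** A reader might infer that the plan analyses self-reports and caregiver reports together. The article does not say so; it is silent on the respondent, and the analysis plan could separate them. This stands. What remains is that separation requires the respondent to have been recorded.
- **The form is not shown.** The questionnaire may already carry such an item: Table 1 is headed a summary, and the mailing includes instructions on filling in the forms. This also stands. The point is that no listed variable does the job, not that the form is known to lack it.
- **Completing a form may mean writing for the patient**, for example after a motor deficit. The self-assessment label fits that reading, under which there may be little bias. The text does not settle it, which is a reason to record scribe and proxy separately.
- **Caregiver presence is not the stated trigger.** A reader might infer that having a caregiver decides who rates. The stated rule is state of health, and availability is only a necessary condition. Since the term is undefined, institutional staff or a visiting relative might count. It is therefore conjecture that an ill patient without a caregiver at home goes missing, and the telephone call also serves as a reminder for unreturned forms.
- **The CIQ-R differs.** It covers home, social and work participation, which another person can observe better than mood, and no validated mode is given for it to contradict.
- **The size is assumed.** Nothing supports a proxy share of 40% or 60%. A share of 10% with a 10-point shift gives an odds ratio of only 1.05, and proxies should be few in the mild stratum.
- **Using only patient-completed forms has its own bias.** It selects patients able to answer, in a cohort meant to describe sequelae across severity. This is a sound argument against making that restriction the main analysis.

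**Conclusion.** The conflict between statements is established: with the validated-mode statement for the HADS and FSS, and with the Table 1 label for all three scales. It is also established that a pathway component under test is a necessary condition for caregiver completion, and that no listed variable identifies the respondent. It follows that associations of caregiver presence, cohabitation and place of life with these outcomes may partly reflect who rated them.

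The document does not show that such bias will occur, or how large it would be or in which direction. The odds ratios of 0.82 to 1.49 rest wholly on an assumed 30% prevalence, assumed proxy shares of 20% to 60% and assumed proxy-rated prevalences of 20% or 45%. Only secondary endpoints are concerned; the mRS at follow-up is collected by research nurses by telephone. The change is worth making because it is cheap and a respondent left unrecorded cannot be recovered in the analysis.

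**What to change.** 1. Add one item to each postal questionnaire, if it is not already there: answered by the patient alone, patient's answers written down by a helper, or caregiver's own judgement.
2. Keep all forms, and report HADS and FSS results by respondent type.
3. Pre-specify a sensitivity analysis limited to patient-answered forms (alone or through a scribe), or adjusted for respondent type. Require it before drawing conclusions on caregiver presence, cohabitation or place of life.
4. Reconcile the validated-mode statement and the Table 1 labels with the follow-up procedure, and say whether a caregiver acts as scribe or proxy.

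The cost is one form item and one extra analysis. The sensitivity analysis will have fewer patients from the severe stratum, and its conclusions will apply only to patients able to answer.

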## Objectives

The main objective of the PAPASéPA project is to identify the life pathways components of stroke patients associated with the activity limitations measured by the Modified Ranking Score (mRS), at 3 months and 1 year after the acute episode.

The secondary objectives are to: 1) identify the life pathways components of stroke patients associated with other types of sequelae (cognitive disorders, anxio-depressive disorders, fatigue, restriction of participation) at 3 months and 1 year after the acute episode; 2) define a typology of the life pathways of stroke patients in Aquitaine, from acute care to 1 year of follow-up and 3) analyze the social and geographical inequalities in the management of stroke in Aquitaine.

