##### Classification of hospitalizations during the following year

For all included patients, the re-hospitalizations in medicine or surgery departments that took place during the year of follow-up will be identified from the SNDS base and classified into three categories: 1) readmission for management of recurrence and post-stroke complications; 2) readjustment for post-stroke follow-up and secondary prevention of stroke and 3) re-hospitalizations to manage a clinical situation not related to stroke.

This classification will be carried out in three stages: 1) automated classification based on ICD-10 codes and procedures associated with readmission, 2) for re-hospitalizations not classifiable in an automated way, the IRC will return to the corresponding patient record, within the hospitalization facility and 3) if it is impossible for IRC to classify rehospitalization, a group of experts (including 3 neurologists and a rehabilitation doctor) will meet to classify each remaining hospitalization, based on the information from the hospitalization report.

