#### Life pathways: perimeter

Despite a collective awareness, as to the inadequacy of the organization of the health system, different realities exist regarding the notion of pathways [38, 44–46].

In the PAPASéPA project, we adopt the global conception of the life pathway of stroke patients. All the elements of care but also the context of life in which the patient evolves (family and social environment, financial aid, income, adaptation of lifestyle and environment, etc.…) will be taken into account.

However, life pathway data are mainly collected during phone interviews using closed-ended questions. Responses may lack of precision and could be not exact. In order to obtain a more precise description of these life pathways access to databases such as the CDAPH (Commission for the rights of disabled persons to independence) would be necessary. This database, which collects all the social benefits people receive, will only be available in the coming years.

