#### Main outcome

The main outcome is the modified Rankin score in three categories. This score gives an overall measure of the level of functional dependence, integrating the ICF components of body function, activity to participation. This is the reference measure found in many publications. Its use in this project will allow national and international comparisons. The defect of reproducibility of its measurement will be taken into account in our project, as following: 1) measure realized by only three people trained according to the good practices of use of the scale before the start of the project, 2) the IRC measuring the mRS during the follow up are not those who included them.

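### The nurse who rates the primary mRS also collects the telephone life-pathway exposures in the same call, and nothing stated keeps the rating independent of them

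*Protocol article*

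**What the plan says.** The Objectives section sets the main aim: to "identify the life pathways components of stroke patients associated with the activity limitations", at 3 months and 1 year. Pathway components are the exposure and the mRS is the outcome.

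Under the ad hoc collection of sequelae and elements of pathways, "This follow-up at 3 months and 1 year will be carried out by the IRCs", by a mailing and a telephone interview. For the interview the text reads: "The information collected will be: 1) life pathway after-stroke data, 2) administration of three specific assessment scales", the mRS being the last of the three scales.

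Table 1 (Data sources) confirms the shared mode. Footnote 5, "Data collected by telephone by the nurse", is attached to the mRS and also to place of life, medical and social care, disability allowances, family or caregiver, walking aids and legal background. Life pathways: perimeter adds that "life pathway data are mainly collected during phone interviews using closed-ended questions".

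Main outcome acknowledges that the mRS is imperfectly reproducible and gives two measures: only three trained people rate it, and "the IRC measuring the mRS during the follow up are not those who included them". Evaluation criteria defines the endpoint as 0–2, 3–5 or 6 (death).

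The only mention of blinding, under Analysis strategy, concerns when the statistical analysis plan is written. It does not concern the rater.

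**The concern.** Whether a patient falls in 0–2 or 3–5 is a judgement about independence. A nurse who learns in the same call that the patient has home services, lives in an institution or uses a walking aid has a cue that may tip a borderline rating. Error of that kind depends on exposure. It can create or inflate an association between a pathway component and dependence, which is what the main objective sets out to estimate.

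The planned analysis would not remove it. The random effect handles the correlation between the two visits, adjustment handles the listed confounders, and a larger sample makes a biased estimate more precise without making it less biased. The two measures in Main outcome act elsewhere: training and few raters limit variability between raters, and a different follow-up nurse removes only what was learned at inclusion.

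**Working it through.** **Inputs from Sample size selection:** independence 51%, dependence 30%, death 19%; alpha 5%; power 80%; odds ratio 2; exposure 20% to 80%; 368 per NIHSS stratum, 1104 in total. The analysis model (proportional odds, three categories) is in the Analysis plan.

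**The plan's own figure.** The proportional-odds sample size formula is N = 3(z_α + z_β)² / [f(1−f)(ln OR)²(1 − Σp³)].

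- Σp³ = 0.51³ + 0.30³ + 0.19³ = 0.1327 + 0.0270 + 0.0069 = 0.1665.
- With f = 0.2 or 0.8 and a two-sided 5% test: 3(1.960 + 0.842)² / [0.16 × 0.4805 × 0.8335] = 367.5, rounded up to 368.
- 3 × 368 = 1104. The figures reproduce, and this point does not change them.

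**Illustration of the bias.** The article gives no rate of misrating, so the share x is an assumption. Take no true association, and let x of the truly independent exposed patients be rated dependent. The unexposed stay at 0.51 / 0.30 / 0.19. The exposed become 0.51(1−x) / (0.30 + 0.51x) / 0.19. Death does not move.

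For x = 10% the exposed are 0.459 / 0.351 / 0.19:
- odds ratio at the 0–2 cut: (0.51/0.49) / (0.459/0.541) = 1.23;
- odds ratio at the death cut: 1.00;
- single proportional-odds estimate, fitted to both cuts: about 1.16;
- among survivors, 0–2 versus 3–5: (0.51/0.30) / (0.459/0.351) = 1.30.

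The rejection rate can be checked by hand with V = n f(1−f)(1 − Σp³)/3 and z = ln(OR)·√V. For n = 368, f = 0.5, x = 10%: V = 368 × 0.25 × 0.8335 / 3 = 25.6; z = ln(1.158) × 5.06 = 0.74; probability beyond ±1.96 is about 11.5%. Simulating the rank test with tie correction (the ordinal test without covariates, two-sided 5%) gives 11.6%.

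Simulated rejection rates, with the range over exposure of 20%, 50% and 80% (highest at 50%):

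| x | Proportional-odds OR | n = 368 | n = 1104 |
|---|---|---|---|
| 2% | 1.03 | about 5% | 5–6% |
| 5% | 1.08 | 6–7% | 8–10% |
| 10% | 1.16 | 9–12% | 18–25% |
| 15% | 1.24–1.25 | 14–20% | 34–49% |

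These figures are for one visit, unadjusted, with the overall 51/30/19 split applied to every stratum. They show scale and do not predict the study's error rate.

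**The case against.** **Order of questions.** A reader might infer from the numbering that the nurse records the pathway first and then rates the mRS. The text does not support this. It lists content, as the inclusion list in the same section does, and fixes no sequence. The call form may sit in an operations manual that an article need not reproduce. That part of the objection stands. What remains is that the article does state that one call collects both, and that Main outcome describes who rates the mRS without a measure directed at this route.

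**Purpose of the safeguards.** Both measures are offered against poor reproducibility, so it would be unfair to call them failed blinding. This is accepted; the point is only that they leave this route open.

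**Scope.** It would be too strong to say that the rater knows the exposure in general. Hospital stays, consultations, paramedical care and drug deliveries come from the SNDS, outside the call. Death needs no judgement.

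**Size.** Collapsing the outcome to independent versus all others gives larger apparent odds ratios (1.11, 1.23 and 1.36 for shifts of 5%, 10% and 15%), but the plan analyses three ordered categories, so those figures should not be used. At a 5% shift within one stratum the effect is close to nil.

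**Nature of the items.** Home help and walking aids are bound up with dependence and may surface in any mRS interview. This is true, and it limits what reordering can achieve. It does not justify leaving the order open.

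**Rehospitalisations.** A reader might extend the point to their classification, since for stays that cannot be classified automatically "the IRC will return to the corresponding patient record". The documents do not support that. The first stage is automated, the last uses an expert group and the hospitalisation report, and nothing says that the mRS is before the classifier.

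**Conclusion.** The concern holds for life-pathway items collected by telephone and for the 0–2 versus 3–5 boundary of the primary mRS. As written, one nurse obtains exposure and outcome in one call, and no stated measure keeps the rating independent of the exposure. This leaves the main-objective associations for those items open to differential rating; it does not show that such rating will occur.

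Size and direction cannot be derived from the article. Under the assumed one-directional shifts, 2% is negligible and 5% matters little within a stratum. At 10%, the false-positive rate is roughly double the nominal 5% at 368 patients and about four to five times nominal at 1104. The results rest on the 51/30/19 split, no true association, a single visit and no covariates. This is a moderate design weakness that should be corrected because the correction is so cheap.

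**What to change.** In the description of the 3-month and 1-year telephone interview, state that the mRS is administered, scored and locked at the start of the call, before any pathway question. State also that at 1 year the rater is not shown the earlier mRS or the earlier pathway answers.

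The cost is a changed call form and restricted display of earlier answers. Sample size, visits and patient burden are unchanged. Some unblinding will remain, because patients may mention help or aids while answering the mRS questions; the report should acknowledge this as a limitation for the telephone-collected exposures.
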